### An ancillary study: the CAPEDP-A Study

Assessment of attachment security and caregiver behaviour being particularly complex from a procedural point of view, an ancillary study involving a subsample of the CAPEDP population was designed to investigate this particular point: the CAPEDP Attachment (CAPEDP-A) Study. The objectives of this ancillary study were to assess the impact of the CAPEDP intervention in terms of increasing infant attachment security and maternal reflexive ability and reducing infant attachment disorganisation and maternal disorganizing behaviour when the child was from 12 to 15 months old.

## Methods/design

The CAPEDP Study is a prospective, randomized controlled, multicenter trial with two parallel arms comparing the CAPEDP intervention to usual care. The trial used Prospective Randomized Open Blinded Endpoint (PROBE) methodology with a 27-month follow-up. Usual care involved access to the PMI and community mental health networks with no out-of-pocket payment, free antenatal maternity screenings, and a variety of social benefits, as described above. The intervention group benefited additionally from the CAPEDP home-visiting program (see below).

### Study population

Eligibility criteria limited participation to mothers in situations of medium to high vulnerability with regard to their future child’s mental health. All consecutive women consulting in the second trimester of pregnancy (from 12 to 27 weeks of amenorrhea) in ten public maternity wards were assessed for eligibility. Pregnant women were eligible if they were: living in the intervention area (Paris and its inner suburbs); sufficiently fluent in French to give valid informed consent, benefit from the intervention and participate in assessment sessions; less than 26 years old; first time mothers; less than 27 weeks pregnant at their first home visit assessment session; eligible for legal national health insurance or its equivalent for non-French participants (as required by French law on clinical research). They also had to declare at least one of the three following criteria: 1) having less than twelve years of education, 2) intending to bring up their child without the presence of the child’s father, and 3) having low income, defined as being eligible for French social welfare health insurance (*Couverture Maladie Universelle Complémentaire*) i.e. with an income less than or equal to 850 euros a month or, for undocumented migrants, Government Medical Aid (*Aide médicale d’Etat*).

Exclusion criteria were: women who would be impossible to follow up, such as Roma, gypsies, travelers, the homeless, or temporary refugees; women already receiving sustained social or medical care for other reasons than the above inclusion criteria (such as addictions or mental or physical disorders requiring close long-term follow-up); and women who did not consent to participate.

Participation in the study was proposed to eligible women in the waiting rooms of each maternity hospital, prior to a prenatal appointment. During this interview or at a second appointment if she asked for more time to make up her mind, the future participant signed the informed consent form.

#### CAPEDP-A subsample

When their child reached 12 months of age, all families participating in the main CAPEDP trial were consecutively invited to participate in the CAPEDP-A study. After receiving information about the study, and if they accepted to participate with their child, mothers signed an informed consent form and an appointment was given to them for a two hour assessment procedure within the following fortnight. Inclusion was terminated when the required 120 mothers had accepted to participate with their child. Mothers received 50 euros gratification for participating in the CAPEDP-A assessment.

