**Method and design:**

The objective of this multicentre randomized controlled parallel trial (PROBE methodology) is to assess the impact in a multi-risk French urban sample of a home-visiting program targeting child mental health and its major determinants. This paper describes the protocol of this study. In the study, pregnant women were eligible if they were: living in the intervention area; able to speak French, less than 26 years old; having their first child; less than 27 weeks of amenorrhea; and if at least one of the following criteria were true: less than twelve years of education, intending to bring up their child without the presence of the child’s father, and 3) low income. Participants were randomized into either the intervention or the control group. All had access to usual care in mother-child centres and community mental health services free of charge in every neighbourhood. Psychologists conducted all home visits, which were planned on a weekly basis from the 7^th^ month of pregnancy and progressively decreasing in frequency until the child’s second birthday. Principle outcome measures included child mental health at 24 months and two major mediating variables for infant mental health: postnatal maternal depression and the quality of the caring environment. A total of 440 families were recruited, of which a subsample of 120 families received specific attachment and caregiver behaviour assessment. Assessment was conducted by an independent assessment team during home visits and, for the attachment study, in a specifically created Attachment Assessment laboratory.

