### Randomisation and masking

After completing baseline screening and informed consent procedures, participants were randomly assigned in a 1:1 ratio to either the CAPEDP intervention or the usual care group using a computer-generated randomisation sequence, stratified by recruitment centre, with random block sizes of 2, 4 or 6 participants. This sequence was centrally generated by the Clinical Research Unit of Bichat Hospital, Paris, France. Assignment of participants was concealed using centralized randomisation through fax in the Clinical Reseach Unit. Investigators thus had no knowledge of the next assignment in the sequence in this open label trial. Investigators, psychologists performing the CAPEDP intervention and participants were blinded to assignment before, but not after, randomisation, as per the open-label design. However, in accordance with PROBE methodology, the outcome assessors were blinded to assignment and no investigators, psychologists or participants had any knowledge of aggregate outcomes at any point during the course of the study.

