##### Secondary analyses

Data that are normally distributed will be analyzed using Student’s t test for continuous data, and chi-square test for categorical data, if the corresponding assumptions are fulfilled. If not, appropriate non-parametric methods will be used. In the intervention group, compliance to the CAPEDP program will be described by the proportion of planned home visits that actually took place performed reported to those scheduled. All statistical analyses will be considered significant at the 5% confidence limit using 2-sided tests. SAS software (version 9.1) will be used for statistical analyses.

More than 5,000 home visits were scheduled. A qualitative and quantitative analysis is being performed on the home visitors’ case notes to evaluate the extent to which the intended intervention program was effectively implemented or not. Case notes are analysed with regard to the frequency of themes that were declared as discussed during each home visit as well as the home visitors’ subjective perceptions of the visit.

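### CAPEDP-A aims to estimate the intervention's impact in 120 dyads who enter at 12 months by a second consent after open-label allocation, so randomisation does not guarantee comparable arms within that subset

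*Protocol article*

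**What the plan says.** The section on the ancillary study gives it a causal aim, to "assess the impact of the CAPEDP intervention in terms of increasing infant attachment security and maternal reflexive ability", together with less attachment disorganisation and less disorganizing maternal behaviour.

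The CAPEDP-A subsample section describes entry. When the child reached 12 months, "all families participating in the main CAPEDP trial were consecutively invited to participate in the CAPEDP-A study". Consent was separate: "if they accepted to participate with their child, mothers signed an informed consent form". Entry then closed on a count: "Inclusion was terminated when the required 120 mothers had accepted to participate with their child". No quota by arm and no second randomisation are stated. Mothers were paid 50 euros for taking part, with no difference by arm stated. The abstract gives the overall numbers: "A total of 440 families were recruited, of which a subsample of 120 families received specific attachment and caregiver behaviour assessment".

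On masking, the Randomisation and masking section says: "Investigators, psychologists performing the CAPEDP intervention and participants were blinded to assignment before, but not after, randomisation". Outcome assessors were blinded, and so were the coders of the laboratory recordings.

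The only between-group tests given beyond the primary outcomes are generic ones under Secondary analyses: Student's t test, and "chi-square test for categorical data, if the corresponding assumptions are fulfilled", with non-parametric methods otherwise. That sentence does not name CAPEDP-A. Multiple imputation is stated under Primary analyses only. The Discussion lists attrition and the modified intention-to-treat set of the main trial as limitations. It does not mention how the subsample is selected.

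**The concern.** Randomisation took place during pregnancy. Entry to CAPEDP-A came about a year after birth and depended on two things that allocation can influence: whether the family was still participating, and whether the mother agreed to a two-hour filmed laboratory assessment.

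The document itself gives reasons why these could differ by arm. Only the intervention arm had the programme visits, which made extensive use of clips of the mother that were filmed and then discussed with her. The sub-study asks for something similar: the dyad is filmed, and for the Insightfulness Assessment the mother watches a clip of herself with her child. The programme also aims to build a working alliance, which could raise willingness. On the other hand, the Discussion notes that visits by psychologists may be felt as stigmatising, which could lower it. What makes a mother stay and accept may well be related to the relationship being measured.

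If selection depends on the outcome differently in the two arms, a comparison of the observed groups mixes the programme's effect with the difference in who entered. That could create an apparent attachment effect or hide a real one. Blinded coding protects the measurement but has no bearing on who enters.

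**Working it through.** **Plan figures.** The article gives no rate, effect size or power for the 120, so that number cannot be reproduced; a condensed article may leave this to the full protocol. As a share of those recruited, 120/440 = 27.3%.

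**Exposure before invitation.** From the section on the intervention, programme visits scheduled by 12 months are 6 (antenatal) + 8 (first three months) + 15 (4 to 12 months) = 29 in the intervention arm and 0 in the control arm. Control families also had home assessment visits by psychologists, so the contrast is in programme visits, not in all contact.

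**Illustration 1: acceptance depends on security.** Assumptions, none from the document: no true effect, 55% secure in both arms, and in one arm only secure dyads accept 1.3 times as often as insecure dyads.

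- Observed secure proportion in that arm = 0.55 × 1.3 / (0.55 × 1.3 + 0.45) = 0.715 / 1.165 = 0.614.
- Observed secure proportion in the other arm = 0.55.
- Spurious difference = 0.614 − 0.55 = 0.064, or 6.4 points, favouring whichever arm has the pattern.
- If the pattern holds in both arms, both show 0.614 and the difference is 0.

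For scale, assume 60 dyads per arm. The standard error of the difference is √(0.614 × 0.386/60 + 0.55 × 0.45/60) ≈ 0.090, so 6.4 points is about 0.7 standard errors.

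**Illustration 2: acceptance depends on a maternal characteristic.** Assumptions: no true effect; half the mothers are in a stratum with 70% secure infants and half in one with 40%; 120 acceptors; normal approximation with a two-sided 5% test. With acceptance a₁ and a₀ in the two strata, the observed secure proportion is (0.5·a₁·0.7 + 0.5·a₀·0.4) / (0.5·a₁ + 0.5·a₀).

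| Intervention a₁/a₀ | Control a₁/a₀ | Secure, intervention | Secure, control | Spurious difference (points) | Type I error | Split of 120 |
|---|---|---|---|---|---|---|
| 0.5/0.3 | 0.5/0.3 | 0.5875 | 0.5875 | 0 | 5.0% | 60/60 |
| 0.5/0.3 | 0.4/0.4 | 0.5875 | 0.55 | +3.75 | 7.0% | 60/60 |
| 0.6/0.3 | 0.4/0.4 | 0.60 | 0.55 | +5.0 | 8.6% | 64/56 |
| 0.6/0.2 | 0.4/0.4 | 0.625 | 0.55 | +7.5 | 13.3% | 60/60 |
| 0.3/0.5 | 0.5/0.3 | 0.5125 | 0.5875 | −7.5 | 13.1% | 60/60 |

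Two things follow. Selection that is the same in both arms does no harm to the comparison under no effect. And an even split of the 120 is no reassurance, because three of the four biased rows give 60/60.

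**The case against.** The strongest reply is that the article does not commit to a naive analysis of CAPEDP-A. The sentence on tests is generic, is conditional on assumptions, and does not name the sub-study; a full plan that is not shown may adjust for entry. This stands. A reader might infer that an unadjusted chi-square is planned for the attachment outcomes, but the document does not say so. What can be said is that none of the tests it does state deals with selective entry.

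A reader might also conclude that the comparison is not randomised. That goes too far. Allocation was randomised; what is lost is its guarantee of comparable groups within a subset formed afterwards. No retention or acceptance rates by arm are given, so bias is plausible but not shown, and it could be nil.

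Nor is 27.3% an acceptance rate. It combines refusals, earlier losses and families whose child reached 12 months after inclusion had closed. Invitation was consecutive, so closing at 120 follows the calendar and mainly limits representativeness. The equal payment may also have reduced differences in refusal.

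Finally, the sub-study is already labelled ancillary, and the main trial already schedules the Attachment Q-Sort (AQS) at 18 months without the subsample mark in Table 1. Both points are correct and reduce the weight of the problem. But the stated aim is still one of impact, and the limitations do not mention this selection.

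**Conclusion.** The point holds in a limited form. The stated entry rule and the stated causal aim do not fit together without qualification: entry follows open-label allocation and depends on retention and a second consent, so comparability of the arms within the 120 cannot be taken from randomisation.

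The size and direction of any bias are unknown. Under the assumed rates above, arm-dependent selection gives spurious differences of about 4 to 7.5 points in either direction and a type I error of about 7% to 13%; selection that is alike in both arms gives none. These figures show what moderate differences in acceptance could do, and are not estimates for this trial.

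The consequence is confined to the Strange Situation Procedure (SSP), AMBIANCE and Insightfulness Assessment (IA) results. The three primary outcomes are untouched. This is a worthwhile, low-cost improvement to what the sub-study can conclude.

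**What to change.** - **Add an analysis that addresses entry.** Beside the simple comparison of SSP, AMBIANCE and IA, weight by the inverse of the probability of sub-study entry, modelled within arm from prenatal, 3-month and 6-month data. If an adjusted outcome model is used instead, keep to prenatal covariates, since the programme can change the later ones. Treat families not reached before closure separately from those who were lost or declined.
- **State its limits.** Weighting can use only families who have these data; the Discussion says that some randomised women withdrew before any were collected. It removes bias only as far as the measured covariates explain the link between entry and outcome. If acceptance depends directly on security, as in the first illustration, part of the bias remains.
- **Describe the selection.** Compare entrants with non-entrants by arm, and report numbers invited, accepting and declining by arm.
- **Word the conclusion accordingly.** Present the CAPEDP-A result as conditional on participation after allocation, and name this among the limitations.
- **Report it alongside the 18-month AQS.** That measure is scheduled for the whole sample and avoids the second-consent filter. It is still subject to attrition, because it needs direct observation at home, and it does not measure disorganisation, maternal behaviour or insightfulness. It therefore complements the laboratory measures and cannot replace them.

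The cost is analysis and reporting work on data the trial already schedules, and some loss of precision from weighting in 120 dyads.

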### Randomisation and masking

After completing baseline screening and informed consent procedures, participants were randomly assigned in a 1:1 ratio to either the CAPEDP intervention or the usual care group using a computer-generated randomisation sequence, stratified by recruitment centre, with random block sizes of 2, 4 or 6 participants. This sequence was centrally generated by the Clinical Research Unit of Bichat Hospital, Paris, France. Assignment of participants was concealed using centralized randomisation through fax in the Clinical Reseach Unit. Investigators thus had no knowledge of the next assignment in the sequence in this open label trial. Investigators, psychologists performing the CAPEDP intervention and participants were blinded to assignment before, but not after, randomisation, as per the open-label design. However, in accordance with PROBE methodology, the outcome assessors were blinded to assignment and no investigators, psychologists or participants had any knowledge of aggregate outcomes at any point during the course of the study.

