### Objectives

The aim of the CAPEDP trial was to evaluate, in young primiparous mothers presenting vulnerability factors associated with greater likelihood of child mental health disorders, the impact on infant mental health of a home-visiting program conducted by trained psychologists and targeting the major modifiable determinants of infant mental health.

The program evaluated three primary outcomes: child mental health at the age of two, as well as two potential mediating variables: maternal postnatal depression at three months postpartum and the quality of the home environment when the child was 12 months old.

Secondary objectives included evaluating the impact of the intervention on: maternal postnatal depression at 6 months postpartum, infant attachment quality at 18 months of age, the mother’s quality of attachment at her child’s second birthday, her knowledge and use of social, medical and educational support services, her perception of receiving support from her own personal network, her parenting perceptions and behaviour, the child’s psychomotor development, sustained withdrawal behaviour of the child at 18 months, the mother’s knowledge concerning child development, her parental stress concerning caring for her child, her access to training and employment, her own psychological health and, in the intervention group, the working alliance between the mother and the home-visiting team (Table 1).

**Table 1 T1:** Outcome criteria and assessment schedule

**Instrument**	**Concept measured**	**Validation**	**Outcome assessor**	**Structure of instrument; scoring**	**Time of measurement**					
			**Place of evaluation**		**Prenatal**	**3 mths after birth**	**6 mths after birth**	**12 mths after birth**	**18 mths after birth**	**24 months after birth**
Edinburgh Post- partum Depression Scale (EPDS)	Pre and pospartum depression	Cox et al., 1987 [40]	Mother during home visits	10 items, 4 point-Likert scales (0–3)	X	X	X	X		
		French validation: Guedeney & Fermanian, 1995 [41]		Range 0–30						
				Higher scores indicate higher levels of depressive symptoms.						
Home Observation for the Measurement of the Environment (HOME) inventory	Quality of the home environment (quality and quantity of stimulation and support available to the child in the home environment)	Bradley & Caldwell, 1979 [42]	Assessment team during home visits	Designed for use during infancy (birth to age three).		X		X	X	

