		French validation Gunning et al, 2004 [43]		45 items (yes/no response)						
				Six subscales:						
				Parental Responsitivity (11 items)						
				Acceptance of the child (8 items)						
				Organization of the environment (6 items)						
				Learning Materials (9 items)						
				Parental Involvement (6 items)						
				Variety in Experience (5 items)						
				Highest scores for each subscale indicate greater environment.						
Child Behavior Checklist 1½-5 (CBCL 1½-5)	Child behavioural disorders	Achenbach 2009 [44]	Assessment team during home visits	100 items, Likert scales (0–2)						X
				Range 0–200						
		French validation: Ivanova et al, 2010 [45]								
				A total score and 7 syndrome scales:						
				Emotionally Reactive (0–18, clinical range (CR) >8)						
				Anxious/Depressed (0–16, CR>8)						
				Somatic Complaints (0–22, CR>6)						
				Withdrawn (0–16, CR >5)						
				Sleep Problems (0–14, CR>8)						
				Attention Problems (0–10, CR>6)						
				Aggressive Behaviour (0–38, CR>24)						
Attachment Q –Sort (AQS)	Child’s attachment	Waters & Deane, 1985 [46]	Assessment team during home visits	Two raters assess each situation, during a home visit of two hours.					X	
		French translation made and validated by a panel of infant mental health experts								
				90 items						
				Correlation with typical secure pattern:						
				Insecure attachment if < 0.35						
				Secure attachment if ≥0.35						
Vulnerable Attachment Style Questionnaire (VASQ)	Mother’s attachment	Bifulco et al., 2003 [47]	Mother during home visit	22 items, 5-point Likert scale (1–5).	X					X
				Range 0–110						
				1 global scale: Vulnerability (0–110, vulnerability if ≥ 57)						
				2 sub-scales:						
				Insecurity (range 0–60, insecure if > 30)						
				Proximity seeking (range 0–50, proximity seeking if ≥ 27)						
Services Questionnaire	Use of social and / or medical services	Specifically designed for this research	Assessment team during home visits	Description of the use of 27 social and / or medical services	X	X	X	X		X
Social Support Interview (SS-A; SS-B)	Perception of social support received and level of satisfaction from the social network	Designed for this research based on Vaux, 1988 [48]	Assessment team during home visits	6 items	X	X		X		X
				Description of social support structure (emotional, material, financial, socialization, valorization)						

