Child mental health at the age of two was assessed using the Child Behavior Checklist 1½-5 (CBCL 1½-5) [70]. This instrument is widely used to assess psychopathology in infants and toddlers. A recent validation study in 23 societies, including the French translation and validation used in the present study, confirmed transcultural validity [45]. It is a 100-item scale, divided into seven syndrome subscales.

Maternal postnatal depression was assessed using the Edinburgh Postnatal Depression Scale (EPDS) [40]. This is a 10-item self-report questionnaire designed to be completed in the presence of an observer. It is valid for assessing both pre- and postpartum depression. The EPDS has been validated in a French population [71]. Different EPDS threshold scores were used to distinguish between depression and major depression.

The quality of the home environment when the child was 12 months old was assessed using the Home Observation for the Measurement of the Environment (HOME) [42]. This is a well-known and widely-used scale assessing the quality and quantity of stimulation and support available to a child in the home environment. As recommended, scoring was conducted during a home visit which did not have scoring the HOME as its unique objective.

Secondary outcome measures are described in Table 1.

The CAPEDP-A study assessed infant attachment quality, maternal disrupting behaviour and parental reflexive capacity using the Insightfulness Assessment (IA) interview.

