### Adherence and withdrawal

Participants were informed that they could withdraw at any time for any reason. In order to optimise adherence to the intervention, families were reminded of upcoming visits by phone or with a text message. Missed home visits were rescheduled within the following week. Home visitors were also encouraged to maintain telephone contact with families between visits. Families that regularly missed home visits or did not respond to phone calls continued to receive regular calls at least once a fortnight from their home visitor. These calls continued through to the end of their planned participation in the study. Letters were regularly sent to each family that had not been in direct contact with their home visitor for a period of over three months without giving news. All participants, including those lost to follow up by the intervention team, were contacted by the evaluation team at every assessment point (at 3, 6, 12, 18, 24 months). In cases where families accepted phone contact but were reticent to receiving any further home visits, assessment took place over the telephone, except for those instruments that required direct observation. If phone contact proved to be impossible, questionnaires were sent to families via the post.

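### The unqualified blinded-assessor statement is wrong for the EPDS, a primary outcome answered by unblinded mothers, and unclear for the CBCL

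*Protocol article*

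**What the plan says.** The design label is general. Methods/design states: "The trial used Prospective Randomized Open Blinded Endpoint (PROBE) methodology with a 27-month follow-up". The Abstract repeats the label. Randomisation and masking then says that "in accordance with PROBE methodology, the outcome assessors were blinded to assignment", without restricting this to particular instruments. The same section says of the mothers that "participants were blinded to assignment before, but not after, randomisation, as per the open-label design".

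Table 1, under Objectives, has a column for the outcome assessor:

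- EPDS: "Mother during home visits".
- HOME and CBCL: "Assessment team during home visits".

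Procedures and outcome measures says of the EPDS: "This is a 10-item self-report questionnaire designed to be completed in the presence of an observer". It does not say who answers the CBCL items.

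Adherence and withdrawal describes a fallback. Families who accept telephone contact but no longer want visits are assessed by telephone, apart from instruments needing direct observation. If the telephone also fails, "questionnaires were sent to families via the post".

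**The concern.** In a PROBE design, treatment is open and credibility rests on the endpoint being judged by someone who does not know the arm. If the person producing the score knows the arm, that protection is absent, however well the visiting psychologist is masked. A blinded observer in the room does not blind a self-report, and with a postal questionnaire there is no observer.

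Differential reporting is plausible here. By the three-month EPDS the programme plans 6 antenatal and 8 postnatal visits, 14 in all, by psychologists trained to build a working alliance; usual-care mothers have no such relationship. Intervention mothers might under-report symptoms to a programme they value, or might disclose more because they have learned to talk about them. Either would shift the EPDS difference without a matching change in depression. The Discussion acknowledges a Hawthorne effect of the evaluation visits, which both arms receive, but not a reporting difference between arms.

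What is at stake is how far a positive EPDS result can be read as prevention of depression when readers have been told that the endpoint was blinded.

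**Working it through.** **Step 1: who produces each primary score**

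| Primary outcome | Assessor in Table 1 | Other text | Blinded as claimed? |
|---|---|---|---|
| EPDS, 3 months | Mother | Called self-report; mothers unblinded after randomisation | No |
| HOME, 12 months | Assessment team | Observation scale, scored at a home visit | Yes, as stated |
| CBCL, 24 months | Assessment team | Informant not named | Unclear |

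The EPDS row needs no inference, because the table and the general statement cannot both hold. For the CBCL, two things raise doubt. Its scales include sleep problems and somatic complaints, which a visitor could hardly rate by watching a child during a visit. And the telephone and postal fallback would cover it if it does not need direct observation. Neither shows who answers at a routine visit.

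**Step 2: the plan's own sample sizes**

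Inputs from Determination of sample size: EPDS SD 4.6, difference 2; HOME SD 4.3, difference 2; CBCL SD 8.95, difference 3; 90% power, two-sided 5%.

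Normal approximation: n per arm = 2 × (1.960 + 1.282)² × (SD/difference)².

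- EPDS: 2 × 10.51 × 2.300² = 111.2, so 112; t-test solution 112.1, so 113.
- HOME: 2 × 10.51 × 2.150² = 97.1, so 98; t-test solution 98.1, so 99.
- CBCL: 2 × 10.51 × 2.983² = 187.0, so 188; t-test solution 188.003, so 189.

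The stated 113, 99 and 189 reproduce, so no figure in the plan is in dispute.

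**Step 3: what a reporting shift could do to the EPDS (illustration)**

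Assume no true effect and a shift of b points in the between-arm difference caused only by reporting. The value of b is an assumption, because the documents give none.

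SE = SD × √(2/n) = 4.6 × √(2/113) = 0.612.

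Rejection rate = Φ(b/SE − 1.96) + Φ(−b/SE − 1.96).

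| b (points) | b/SE | Significant result |
|---|---|---|
| 0 | 0 | 5.0% |
| 0.5 | 0.817 | 12.9% |
| 1 | 1.634 | 37.2% |
| 2 | 3.268 | 90.5% |

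The last row is simply the design power, since a 2-point shift equals the target difference.

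**Step 4: the shift that would cancel a result**

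Suppose the trial observed exactly the 2-point EPDS reduction with 113 per arm and SD 4.6. The 95% interval would be 2 ± 1.96 × 0.612, that is 0.80 to 3.20. A reporting shift of 0.80 points would bring the nearer limit to zero, and one of 2 points would bring the estimate to zero. This needs no assumed bias, and readers can judge for themselves whether such a shift is credible.

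**The case against.** The best defence is that the statement was meant for the assessment team: four psychologists working independently of the home visitors, with no prior knowledge of the arm. For them it is accurate. Nothing is hidden either: the same section says that participants are unblinded, and Table 1 and the text disclose the self-report. Self-report is also a legitimate way to measure depressive symptoms. All of this stands. It makes the problem one of an overbroad claim rather than a bad choice of instrument. It does not rescue the claim, because the article's own column names the mother as the assessor of a primary endpoint.

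Three stronger readings are tempting, and the documents do not support them.

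- A reader might infer that the CBCL is also unblinded maternal report, so that at most one primary outcome of three is protected. Table 1 separates instruments completed by the mother from those of the assessment team and puts the CBCL with the latter. The telephone and postal route is a fallback for families who decline visits, and it does not name the CBCL. Maternal report is an inference, and not a stated fact.
- A reader might take the percentages as the expected false-positive rate. They follow entirely from the assumed shift, and the direction is also unknown: fuller disclosure by supported mothers would work against the programme.
- A reader might want an EPDS result accepted only if the HOME at 12 months and the ADBB and AQS at 18 months agree. Those measure other constructs, 9 to 15 months later. If depression improved and those three did not change, all three would agree in direction by chance in (1/2)³ = 1/8 of trials, assuming independence. Such a rule would usually deny a real effect.

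A calculation of the cancelling shift may already be in an analysis plan that is not shown. Its absence from the article is not the complaint.

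**Conclusion.** The point holds for the EPDS and rests on the text alone: one of three primary endpoints lacks a property that the article claims without exception. For the CBCL, blinding is unclear and needs only a statement of who answers and how. The HOME is blinded as far as the article states. The sample sizes are correct. The illustrative rates of about 13%, 37% and 90% show that shifts at or below the 2-point target could produce significance with no true effect. They rest on an SD of 4.6, 113 per arm and assumed shifts, and they are no evidence that such bias occurred. The practical consequence is limited: the wording, the list of limitations and the strength of an EPDS conclusion should change. The choice of instrument and the test need not.

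**What to change.** 1. In the Abstract, Methods/design and Randomisation and masking, restrict the blinded-endpoint statement to instruments rated by the assessment team. Among the primary outcomes, that is clearly only the HOME.
2. State that the EPDS is maternal self-report by participants who know their arm.
3. Name the CBCL informant and the mode of completion. If the informant is the mother, treat the CBCL in the same way as the EPDS.
4. Add differential reporting between arms to the limitations, beside the Hawthorne effect, and say that its direction is unknown.
5. Report any positive EPDS result, and any positive CBCL result if mother-reported, with the reporting shift in points that would bring the estimate, and then its nearer confidence limit, to zero. Interpret it alongside the observer-rated outcomes, without making it conditional on them.

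This needs no new data: some wording and one short calculation per affected outcome. The price is a more guarded EPDS conclusion.
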